#### Allocation concealment mechanism

The allocation will be made based on clusters, which is community aged care areas, rather than individuals. A RA ([name]) from the research group will allocate the individual older adults by pre-recruitment and baseline screening, using a parallel design. The clusters will be identified before randomization of the individual participants. The cluster allocation will be going forward from a list of meals-on-wheels receivers from the municipality kitchen meeting the inclusion criteria within the clusters. Allocation concealment is not possible. After identifying the individual older person, a second RA ([name]), will contact the identified older person by phone for recruitment to the study.

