### Participants

This study will use two sets of eligibility criteria, respectively for the community aged care areas (clusters) and the individual participants.

Community aged care groups (clusters): The citizens who need health care in The City of Odense are placed in a total of five community aged care areas. Excepted are those suffering from severe dementia, brain injury and mental illness, who receive special health care treatment outside the community aged care areas. All five community aged care areas will randomly be assigned into two clusters. The Intervention cluster consists of three community aged care areas: Dalum, Tagtaekker, and Skibhus, and the Control cluster consist of two community aged care areas: Rugaard, and Munkebjerg.

Inclusion and exclusion criteria for the individual participants:Inclusion criteriaCommunity-dwelling older adults (65+ years of age)Receiving meals-on-wheels (at least one time per/week) from the municipal supplier at the time of recruitmentLive in The City of OdenseExclusion criteriaModerate/severe dementia assessed by the community Health Care StaffBeing deaf and/or not understand the language of DanishNot being able to sign the informed consentReceiving (or likely to receive in the next 6 months) enteral tube feeding or parenteral nutrition;Participating in other project in the municipality about nutritional support in the form of dietetic adviceReceiving meals-on-wheels from a private supplier at the time of recruitmentOn an end-of-life care pathway

The reason for exclusion of older adults being deaf or not speaking Danish language is that the project has limited funding for translation into different languages, and it will not be possible to hire a deaf interpreter. It is, however, estimated by the researchers involved, that only a few will be excluded due to this reason.

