### Randomization

#### Sequence generation

A cluster randomized trial design is used, with community aged care areas, as clusters of randomization. The two clusters were randomly assigned, and it was decided at a above level of the organization in The City of Odense, not knowing about this study, which community aged care areas that should be allocated into the intervention group and the control group. The decision was made in consideration of which community aged care areas was next in having their Health Care Staff participating in the first part of the intervention; the education of the Health Care staff. The prospective participating community aged care areas will be provided with verbal information and full explanation of the trials by an RA ([name]). No written consent form is signed by the community aged care areas.

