#### Implementation

Initial eligibility screening will be conducted by several RA’s. First by an eligibility screen in the municipality care system, over the phone, and later in the participant’s home. One RA ([name]) will review the study protocol in detail with the potential participant and conducts an eligibility screen in the municipality care system to verify if the individual meets the inclusion or exclusion criteria. Another RA ([name]) will confirm that the participant is interested in participating in the study over the phone. If so, a time will be scheduled to visit the participant’s home. While in the home, a RA will obtain written informed consent from the participant agreeing to participate in the study. If the participant agrees to participate a comprehensive baseline assessment is then obtained to gather outcome measures.

For practical reasons, the intervention cluster will first be included during a period of 10 weeks or until the number needed according to the power calculation and then the control cluster will be included during a period of 10 weeks or until the number needed according to the power calculation.

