#### Blinding

An RA from the manager group in The City of Odense performing the allocation of clusters has no contact with the community aged care groups and will be blinded from all aspects of allocation and subsequent intervention. Participants, Care Managers/RD’s, the principal investigator ([name]) and RA’s ([name]) will not be blinded for the intervention. Data will be analyzed by an external RA, who will be blinded for the results of randomization.

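### Recruiters who know the arm recruit, consent and baseline-assess participants, so the between-arm comparison is open to recruitment bias, and the blanket statement that concealment is impossible is too broad

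*Protocol article*

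**What the plan says.** All references are to the protocol article.

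- **Participants** names the areas by arm: "The Intervention cluster consists of three community aged care areas: Dalum, Tagtaekker, and Skibhus, and the Control cluster consist of two community aged care areas" (the two control areas are then named).
- **Sequence generation** says that municipal management chose the areas: "The decision was made in consideration of which community aged care areas was next in having their Health Care Staff participating in the first part", which is the staff education.
- **Allocation concealment mechanism** gives the order: "The clusters will be identified before randomization of the individual participants". Candidates come from "a list of meals-on-wheels receivers from the municipality kitchen meeting the inclusion criteria within the clusters". A second research assistant "will contact the identified older person by phone for recruitment to the study". The same section states "Allocation concealment is not possible".
- **Implementation** has eligibility screened in the care system, by phone and in the home. One research assistant "will review the study protocol in detail with the potential participant". Written consent is taken at the home visit and baseline follows. The intervention areas are recruited first, for 10 weeks or until the required number is reached, and the control areas afterwards on the same rule.
- **Blinding** says that participants, case managers, the principal investigator and the named research assistants "will not be blinded for the intervention". **Outcomes** adds that the assessors cannot be blinded.
- **Background** sets the second aim as a comparison with usual care. **Analysis** confirms the wish to explore a difference between groups, using tests of change and a model with cluster as a random effect.

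**The concern.** In a cluster trial, allocating areas at random or otherwise does not protect the comparison if individuals enter after the arm is known. Whoever screens and invites can then, without intending it, bring different kinds of people into the two arms. If candidates also know their arm, acceptance can differ too. The intervention involves goal setting and activities such as shopping and cooking over eight weeks, while control participants continue usual care and are measured.

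The second aim is at stake. A difference in quality of life or chair stand at follow-up could partly reflect who was recruited. The pilot is also meant to inform a definitive trial, so an unexplained statement that concealment is impossible could be carried into that design. The limitations sections do not mention recruitment bias.

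**Working it through.** The plan has no figure of its own on this point. The main check is the order of events, followed by a scale illustration.

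**Order of events**
1. Areas are assigned to named arms (Participants; Sequence generation).
2. Individuals are identified from the kitchen list within allocated areas (Allocation concealment mechanism).
3. They are screened, phoned, informed and consented, and then measured at baseline (Implementation).
4. Staff education, the first part of the intervention, begins only once baseline is finished (Preparation of the intervention).

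Steps 2 and 3 are done by unblinded research assistants. The sequential recruitment means that the arm also follows from the calendar period. Two features leave room for judgement: eligibility is screened at three stages, and the dementia exclusion is assessed by community health care staff.

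**Does the analysis remove it?** The t-test, Mann-Whitney and Chi2 tests compare the people recruited as they stand. A random effect for area allows for correlation within an area. Each area belongs wholly to one arm, so a systematic recruitment difference between arms lies in the arm contrast and the random effect does not absorb it. Comparing changes removes a level difference that stays constant over time. It does not remove a difference in prognosis or motivation that affects the change itself.

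**Must participants know the arm before baseline?** Step 4 shows that nothing is delivered before baseline. The candidate list already exists. The documents give no reason for earlier disclosure.

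**Scale, illustration only**
- Inputs from Sample size: 53 per group, and 0.222 and 0.355 read as SDs. The 53 is taken as given.
- Pooled SD = √((0.222² + 0.355²)/2) = 0.296.
- SE of the difference = 0.296 × √(2/53) = 0.0575. Individuals are treated as independent, as that section's statement about clusters implies.
- With no true effect and a recruitment shift b, the two-sided 5% test rejects with probability Φ(b/SE − 1.96) + Φ(−b/SE − 1.96).

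| Assumed shift b (EQ-5D) | b/SE | Rejection rate |
|---|---|---|
| 0 | 0 | 5% |
| 0.02 | 0.35 | 6% |
| 0.05 | 0.87 | 14% |
| 0.10 | 1.74 | 41% |
| 0.15 | 2.61 | 74% |

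The shifts are assumptions and none comes from the documents. The SD is that of follow-up scores. For an analysis of change, b is the shift that survives in the change, and the SD of change is not given.

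**The case against.** The strongest reply is that the concealment sentence is accurate for its likely meaning: with areas assigned in advance and unblinded recruiters, the arm cannot be hidden from those who recruit. This is also a pilot. Its primary outcome is completeness of data and information on sample size, and the between-arm analysis is exploratory. Refusal counts and baseline adjustment are often left to a fuller document, so their absence from an article would not by itself be a finding.

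Much of this stands, and it limits the point. Several stronger readings are tempting but unsupported:
- **That candidates are told their arm before consent.** A reader might infer this from the protocol review and the lack of blinding. No sentence says so; the review could describe both arms, and consent material is not shown. Only the recruiters' knowledge is clear.
- **That people choose their arm.** The area fixes the arm. What can differ is who is invited and who accepts.
- **That recruiters pick names freely.** The text says they work forward from a list and leaves the order unspecified.
- **That few of the 1477 recipients are needed, so selection must be strong.** That ratio is not an acceptance rate, and the 1477 include people under 65 and others who are ineligible.
- **That full concealment is feasible.** Sequential recruitment by unblinded staff limits what can be achieved.

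The reply does not answer why participants could not remain uninformed of their arm until after baseline. Nor does it remove the risk to an aim that the protocol itself states.

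**Conclusion.** The point holds in limited form. The documented order exposes the second-aim comparison to recruitment bias of unknown size and direction, and the planned tests and random effect do not remove it. A reader might conclude that the comparison is biased, or that the completeness ratios are compromised. The documents support neither: the first is a risk and not a demonstrated fact, and the primary feasibility outcome is less exposed.

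The concealment statement is too broad. It may be right for recruiters, but no reason is given for participants. That delayed disclosure would work here is a design judgement, resting on the existing list and on education starting only after baseline. The rejection rates of 14% and 41% show what shifts of 0.05 and 0.10 would do; they do not estimate what will happen.

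**What to change.** Replace the sentence on concealment with a rule:
1. Eligible people on the kitchen list are approached in a pre-drawn random order within each area.
2. One identical script and consent text is used in all five areas. It says truthfully that areas are already allocated and that the person's arm will be disclosed after the baseline visit.
3. The arm is disclosed only once baseline is complete.

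Recruit the areas concurrently if practicable. If the sequential order in Implementation stays, state recruitment bias as a limitation.

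Report by arm the numbers approached, refusing, and declining after disclosure. In the random-effect model already planned, adjust the between-arm comparison for the baseline value of each outcome, and do not rely on unadjusted tests of change. Baseline values are already collected for every outcome in Table 1.

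The cost is a random ordering of an existing list, one shared text and a simple count. Concurrent recruitment would cost more, because the sequence was chosen for practical reasons. Some intervention participants may decline after disclosure; they are recorded as non-uptake, which a pilot should measure. Concealment stays partial while the research assistants know the arm, and baseline adjustment corrects only for differences that the baseline measures capture.

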#### Implementation

Initial eligibility screening will be conducted by several RA’s. First by an eligibility screen in the municipality care system, over the phone, and later in the participant’s home. One RA ([name]) will review the study protocol in detail with the potential participant and conducts an eligibility screen in the municipality care system to verify if the individual meets the inclusion or exclusion criteria. Another RA ([name]) will confirm that the participant is interested in participating in the study over the phone. If so, a time will be scheduled to visit the participant’s home. While in the home, a RA will obtain written informed consent from the participant agreeing to participate in the study. If the participant agrees to participate a comprehensive baseline assessment is then obtained to gather outcome measures.

For practical reasons, the intervention cluster will first be included during a period of 10 weeks or until the number needed according to the power calculation and then the control cluster will be included during a period of 10 weeks or until the number needed according to the power calculation.

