**Methods:**

This cluster randomized controlled study will consist of two clusters of a total of 5 community aged care areas; the intervention cluster, which hold 3 community aged care areas and the control cluster which hold 2 areas. The 130 community-dwelling older adults, receiving meals-on-wheels, will randomly be allocated to either the intervention cluster consisting of 8 weeks of participation in a rehabilitation program led by a Case Manager or the control cluster receiving usual community aged care. The primary outcome will be assessment of data collection (ratio between completed- and non-completed data) and assessment of sample size. The secondary clinical outcomes will be health-related quality of life (EQ-5D-3 L), muscle strength (chair stand), nutritional status (weight/BMI), loneliness (UCLA scale), mental well-being (Warwich-Edinburgh scale), self-efficacy (General Self-Efficacy scale), satisfaction with food-related life (SWFL scale) and refrigerator content.

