### Outcomes

The outcome assessments, conducted in the participants homes by Research Assistants (RA) and Case Managers/RD’s will occur at inclusion (Baseline, *t* = 0) and at the end of the intervention period (Follow-up, *t* = 2). At the beginning of second part of the intervention some outcome assessments will also be conducted in only the Intervention cluster (In between, *t* = 1). It is, however, not obtained by the same person at baseline, in between, and follow-up for practical reasons. However, all will receive the same training in the methods on obtaining outcome assessments by RA ([name]) or RA ([name]). Due to the design of the study it is not possible to blind neither the RA’s nor the Case Managers/RD’s. An overview of the outcome measurements is presented in Table 1 and described in detail below.

**Table 1 Tab1:** Data collection 2 Content in fridge (sufficient, insufficient, empty)

Measure	Time of data collection		
	Baseline *T* = 0	In between *T* = 1	Follow-up *T* = 2
Quality of life by EQ-5D-3 L	X	X	X
Height, meter	X	X	X
Weight, kg	X	X	X
BMI, (kg*kg/m2)	X	X	X
Muscle strength - Chair stand^1^	X	X	X
Satisfaction with food-related life	X	X	X
UCLA Loneliness Scale	X		X
The Short Warwich-Edinburgh Mental Well-being Scale	X		X
General Self Efficacy Scale	X		X
Refrigerator content^2^	X		X
Sociodemographic	X		
Meals-on-wheels (days/w)	X		

^1^Rise from a chair without using the arms in 30 s

^2^Content in fridge (sufficient, insufficient, empty)

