### Sample size

As this is a pilot trial the primary outcome is understanding the feasibility of implementing a large-scale trial. However, to determine sample size for sufficient power to evaluate developmental trajectories of our secondary outcome variables population estimates were derived using data from Beck et al. [42] who had the same design, population and outcome (quality of life by means of EQ-5D-3 L) as in the present study and showed a significant difference between intervention and control group in the EQ-5D-3 L follow-up score of (0.758 [0.222] versus 0.534 [0.355], (*P* = 0.001). Here it was found that the variation seen in quality of life was due to residual variation (the variation from individual to individual) and was not dependent on the clusters. Hence, with a statistical significance level of 0.05 and a power of 80% app. 53 is needed in each group. Estimating a drop-out rate of 20%, due to a longer intervention period than the former study [42], app. 130 participants are needed. This number could probably be included in approximately 10 weeks, for respectively control and intervention group.

The sample size for this trial will be compared with the actually collected samples as to estimate the required sample size for a future cluster randomized trial.

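### Recruiting the whole intervention arm before the whole control arm confounds the secondary between-arm comparison with calendar period, and the protocol does not acknowledge it

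*Protocol article*

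**What the plan says.** The order of recruitment is fixed in the protocol article under Randomization, Implementation. Giving only practical reasons, it states that "the intervention cluster will first be included during a period of 10 weeks or until the number needed according to the power calculation", and continues: "then the control cluster will be included during a period of 10 weeks or until the number needed according to the power calculation". The Sample size section agrees, giving each group its own window: "This number could probably be included in approximately 10 weeks, for respectively control and intervention group".

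Under Outcomes, the assessments "will occur at inclusion (Baseline" and again at the end of the intervention period, so baseline dates follow recruitment dates. The intervention arm has "8 weeks of participation in a rehabilitation program led by a Case Manager", preceded by staff education that starts once baseline assessments are finished.

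The Allocation concealment mechanism section says that individuals are allocated "by pre-recruitment and baseline screening, using a parallel design". The Analysis section compares changes within and between groups by t-test, Mann-Whitney U or chi-squared test, and adds a model with cluster as a random effect. The limitations do not mention the recruitment order.

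**The concern.** The second aim in the Background is to learn whether quality of life and muscle strength improve relative to usual care. The sample size is built on a between-arm EQ-5D-3L difference. Both need the two arms to be observed under the same conditions, apart from the intervention.

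Here one arm enters entirely in the first window and the other entirely in the second. Season, changes in municipal services, and changes in who assesses and how experienced they are can all differ between windows. The Outcomes section raises the last possibility itself: assessors are unblinded and are not the same person at each time point, although they share common training. At stake is whether a between-arm difference in the secondary outcomes can be read as an effect of the programme.

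**Working it through.** **Timing.** Inputs: two consecutive windows of up to 10 weeks (Implementation, Sample size) and baseline at inclusion (Outcomes). Even accrual and full windows are assumptions.

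- Intervention baselines: weeks 0 to 10, midpoint week 5. Control baselines: weeks 10 to 20, midpoint week 15.
- Overlap: 0 weeks. Lag between mean dates: 15 − 5 = 10 weeks.
- If the windows close early after w1 and w2 weeks, the lag is (w1 + w2)/2. It shortens, but overlap stays 0.
- With a common interval of L weeks to follow-up, the follow-up windows are L to 10 + L and 10 + L to 20 + L. Overlap is again 0.

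**What a trend does.** Let f(t) be the mean outcome at calendar week t with no treatment effect. Bias is intervention minus control.

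- Linear trend, f = bt. Changes: bL − bL = 0. Follow-up scores: b(5 + L) − b(15 + L) = −10b.
- Trend with changing slope, f = ct². The change for a person entering at t is c(2tL + L²). The arm means are c(10L + L²) and c(30L + L²), so the bias in change is −20cL.
- Unequal intervals L1 and L2 could let the follow-up windows overlap in part, but even a linear trend then leaves b(L1 − L2) in the difference in change.

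**Can the analysis separate them?** A period indicator would equal the arm indicator for every participant. The random cluster effect does not help, because each area lies wholly in one arm and one period.

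**Illustrative size, follow-up scores only.** The documents give no period effect, so the shifts below are assumptions. From Sample size: planned difference 0.758 − 0.534 = 0.224; SDs 0.222 and 0.355, pooled √((0.222² + 0.355²)/2) = 0.296; 53 per group. With these inputs, two-sided 0.05 and 80% power, 2 × 0.296² × (1.960 + 0.842)² / 0.224² gives 28 per group. The stated 53 is therefore not reproduced; that is a separate matter, and 53 is used here as stated. SE = 0.296 × √(2/53) = 0.0575. The false-positive rate is Φ(−1.96 + b/SE) + Φ(−1.96 − b/SE), with b now the level shift, no true effect and no clustering.

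| Assumed level shift | Share of 0.224 | False-positive rate (nominal 5%) |
|---|---|---|
| 0.02 | 9% | 6% |
| 0.05 | 22% | 14% |
| 0.10 | 45% | 41% |

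The bias equals the shift and does not shrink with more participants. These rates do not apply to changes, where a stable level shift cancels.

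**Check of an interleaved order.** Blocks: intervention 0–3.33, control 3.33–8.33, intervention 8.33–11.67, control 11.67–16.67, intervention 16.67–20.

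- Intervention midpoints 1.67, 10 and 18.33: mean 10. Control midpoints 5.83 and 14.17: mean 10. Lag 0.
- With equal mean entry dates, the −10b and −20cL terms above both become 0.
- Assuming 130/2 = 65 per arm, the pace is 65/10 = 6.5 per week throughout, as planned. Equal 4-week blocks would give the two control areas only 8 weeks: 65/8 = 8.1 per week, 25% faster.

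**The case against.** The strongest defence is that this is a pilot. The primary outcome is the ratio of completed to non-completed measures, estimated with a 95% confidence interval, and the protocol states no between-arm comparison of it. The Analysis section presents the group comparison as exploratory. Changes over equal intervals also cancel a steady trend and any stable difference between windows. All of this stands, and it limits the point to the secondary comparison. It does not remove the point, because that comparison is a stated aim and a trend need not have the same slope in both windows.

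A reader might go further in four ways that the documents do not support:

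- **That the order contradicts the design.** The word parallel can mean simply parallel-group, not crossover, and sequential inclusion does not breach that. Because it is attached to pre-recruitment and screening, the wording needs clarifying, but it is not a proven contradiction.
- **That any drift biases the result.** The linear case above shows otherwise for changes over equal intervals.
- **That the feasibility results are compromised.** Completion within each arm can still be estimated; only a contrast of completion between arms would mix arm with period.
- **That the order causes recruiters to know the arm.** That knowledge comes from allocating the areas beforehand. The protocol says openly that "Allocation concealment is not possible", and changing the order would not alter this.

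**Conclusion.** The point holds for the secondary between-arm comparison. Arm and recruitment period coincide completely, no model can separate them, and the limitations do not say so. The firm figures are zero weeks of baseline overlap and, assuming full windows and even accrual, a lag of about 10 weeks between mean recruitment dates. The absence of follow-up overlap rests on equal intervals in the two arms. The size and direction of any bias cannot be learned from the documents; the tabulated shifts only illustrate the follow-up-score case. The primary completion ratios are largely unaffected.

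**What to change.** Within the same 20 weeks and with the same staff, recruit the areas in the order intervention, control, intervention, control, intervention. Use blocks of about 3.3 weeks per intervention area and 5 weeks per control area, so that each arm keeps 10 weeks and both have a mean recruitment date of week 10. Apply the protocol's own rule on education area by area: it starts in an intervention area once that area's baselines are complete. This balances linear trends in follow-up scores and simple curvature in changes; it does not guarantee removal of every irregular period effect.

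The cost is scheduling. Education must be arranged area by area, and Sequence generation ties the choice of areas to a municipal education calendar decided outside the study, so the municipality must agree. Each area's recruitment is also compressed into one block. No extra visits are needed.

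If this cannot be arranged, state the confounding of arm with period as a limitation and do not attribute between-arm differences to the intervention. In either case, say under Allocation concealment mechanism what parallel design means, and reconcile it with Implementation.
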